## Abstract

**Background:**

Multiple observational studies have associated metformin prescription with reduced progression of abdominal aortic aneurysm (AAA). The Metformin Aneurysm Trial (MAT) will test whether metformin reduces the risk of AAA rupture-related mortality or requirement for AAA surgery (AAA events) in people with asymptomatic aneurysms.

**Methods:**

MAT is an international, multi-centre, prospective, parallel-group, randomised, placebo-controlled trial. Participants must have an asymptomatic AAA measuring at least 35 mm in maximum diameter, no diabetes, no contraindication to metformin and no current plans for surgical repair. The double-blind period is preceded by a 6-week, single-blind, active run-in phase in which all potential participants receive metformin. Only patients tolerating metformin by taking at least 80% of allocated medication will enter the trial and be randomised to 1500 mg of metformin XR or an identical placebo. The primary outcome is the proportion of AAA events defined as rupture-related mortality or need for surgical repair. Secondary outcomes include AAA growth, major adverse cardiovascular events and health-related quality of life. In order to test if metformin reduced the risk of AAA events by at least 25%, 616 primary outcome events will be required (power 90%, alpha 0.05).

**Discussion:**

Currently, there is no drug therapy for AAA. Past trials have found no convincing evidence of the benefit of multiple blood pressure lowering, antibiotics, a mast cell inhibitor, an anti-platelet drug and a lipid-lowering medication on AAA growth. MAT is one of a number of trials now ongoing testing metformin for AAA. MAT, unlike these other trials, is designed to test the effect of metformin on AAA events. The international collaboration needed for MAT will be challenging to achieve given the current COVID-19 pandemic. If this challenge can be overcome, MAT will represent a trial unique within the AAA field in its large size and design.

**Trial registration:**

Australian Clinical Trials ACTRN12618001707257. Registered on 16 October 2018

## Summary

Note: the numbers in curly brackets in this protocol refer to SPIRIT checklist item numbers. The order of the items has been modified to group similar items.

## Introduction

### Background and rationale {6a}

Abdominal aortic aneurysm (AAA) rupture is an important cause of death in older adults [1]. Most AAAs are identified by incidental imaging or screening when they are small, asymptomatic and at low risk of rupture [2]. Up to 70% of small asymptomatic AAAs expand in size over time to ≥55 mm when the risk of rupture increases [2, 3]. The only established way to prevent AAA rupture is elective repair by open or endovascular surgery [4, 5]. Randomised controlled trials have shown that elective surgical repair of small (< 55 mm) asymptomatic AAAs does not reduce mortality [6]. Clinical guidelines recommend that small (< 50 mm in women and < 55 mm in men) asymptomatic AAAs are managed conservatively by repeat imaging surveillance until they reach threshold diameter when surgical repair should be considered [4, 5]. Since most non-surgically managed AAAs continue to grow in size until they reach the threshold for surgical repair, there is an unmet need to identify drug therapies able to limit AAA progression [2].

Previous randomised clinical trials have tested the efficacy of blood pressure-lowering agents [7–10], antibiotics [11–16], the mast cell inhibitor pemirolast [17], the anti-platelet inhibitor ticagrelor [18] and the fibrate fenofibrate [19], to slow AAA growth [20]. None of these trials has demonstrated a benefit of tested medications in limiting AAA growth. Important limitations of these past trials have included small sample sizes, short follow-up and a focus on imaging findings rather than clinically important outcomes [20–22].

Multiple observational studies have identified inverse associations of diabetes with AAA prevalence and AAA growth [23, 24]. These observations are contrary to the strong positive association of diabetes with other vascular diseases and their complications [25]. The Life Line Screening Study paradoxically reported that higher blood glucose levels were positively associated with the risk of AAA in people who did not have diabetes, whereas AAA risk was significantly lower for those with a confirmed diabetes diagnosis [26]. This finding suggests that the reduced prevalence of AAA in people diagnosed with diabetes may not be attributable to a protective effect of hyperglycaemia but rather may be a consequence of medication used to treat diabetes. Metformin is the longest established treatment for diabetes, and previous rodent studies have suggested that metformin limits pathological mechanisms such as inflammation and matrix remodelling implicated in AAA [27–29]. Several human observational studies have reported an association of metformin with reduced AAA growth [27, 30–32]. A meta-analysis of eight studies including 153,553 patients reported that metformin prescription was associated with a weighted mean reduction in AAA growth of 0.8 mm/year (95% confidence interval, *CI*, 0.5 to 1.1). A meta-analysis of a further three studies including 13,016 patients suggested that metformin prescription was associated with a reduction in the risk of AAA rupture-related mortality and AAA repair (AAA events; relative risk, *RR*, 0.60, 95% *CI* 0.50 to 0.71).

These data provide a strong rationale for anticipating beneficial effects of metformin in reducing the incidence of clinically important events in people with an AAA amongst whom there are no current plans for surgical repair. The Metformin Aneurysm Trial (MAT) will define the effects of metformin compared to placebo on the risk of AAA events in patients with an AAA measuring 35 mm or greater.

### Objectives {7}

The primary aim is to assess whether a daily dose of 1500 mg metformin extended release (XR) compared to placebo reduces the risk of AAA rupture-related mortality or surgical repair. The secondary aims are to assess the effects on AAA growth, major adverse cardiovascular events (MACE), health-related quality of life and requirement for peripheral vascular surgical procedures.

### Trial design {8}

MAT is an international, multi-centre, prospective, parallel-group, randomised, double-blind, placebo-controlled phase 3b trial. The double-blind period will be preceded by a 6-week, single-blind (participants are blinded), active run-in phase in which all potential participants receive metformin XR with fortnightly dose up-titration (Fig. 1). The aim of this run-in phase is to promote the randomisation of participants who tolerate the treatment regimen and to increase the likelihood of high treatment adherence during long-term follow-up. It is anticipated that randomised participants will receive study medication for a mean of 3.5 years. All participants will be asked to continue the study drug until the trial is completed.

**Fig. 1 Fig1:**
[figure not shown]
Study schema

## Methods: participants, interventions and outcomes

### Study setting {9}

MAT will be conducted across multiple international sites. At this stage, two sites in New Zealand and seven sites in Australia have been activated.

### Eligibility criteria {10}

#### Inclusion criteria

An infrarenal AAA with a diameter of ≥35 mm on imaging with the treating doctor indicating that repair is not currently plannedThe participant must be at least 18 years old and provide written informed consent

#### Exclusion criteria

Symptomatic, ruptured or infected AAAPrevious abdominal aortic surgery including abdominal aortic bypass, endarterectomy or repairContraindications to metformin, including:
Renal impairment (eGFR < 45 ml/min/1.73m^2^)Liver cirrhosis (current or previous diagnosis)Severe heart failure: defined as New York Heart Association Class IV, requiring in-patient treatment within the last 12 months or leading to shortness of breath at restBinge alcohol use defined as consuming 5 or more drinks (male), or 4 or more drinks (female), in 2 hPrevious allergic reaction to metformin [33–35]Current indication for metformin (i.e. diabetes defined by HbA1c ≥6.5%) [36]Involvement in another drug trialTerminal illness

### Who will take informed consent {26a}

Written informed consent must be obtained in accordance with Good Clinical Practice (GCP) from all participants before conducting any study procedures including screening assessments. Consent will be obtained by an approved researcher with appropriate training in good clinical practice. This will be obtained prior to screening. The participant information sheet and consent form (PISCF) signed by the participant and the authorised person conducting the consent process must be the current ethics committee (EC)/institutional review board (IRB)-approved version. The complete original signed (PISCF) must be filed in the patient’s study file. A copy must be provided to the participant. Prospective participants will be informed that the screening and run-in phase will determine eligibility for the study and that signing the PISCF does not guarantee enrolment into the study.

### Interventions

#### Explanation for the choice of comparator {6b}

The comparator will be inactive placebo identical to the intervention in all aspects. This comparator has been chosen since currently no medication has been shown to be effective in limiting AAA progression.

#### Intervention description {11a}

Participants who successfully complete the run-in phase and who meet eligibility criteria for study continuation will be randomised to receive:
i.Metformin XR: 3 × 500 mg tablets per day*Or*ii.Matched placebo: 3 × 500 mg tablets per day

The study drug will be administered orally once daily with water. Participants will be advised to take the study drug with their evening meal. If a dose is missed, participants will be advised to take the study drug as soon as they remember. However, it will be made clear to participants that a double dose should not be taken on the same day. The study treatment is double-blinded.

#### Criteria for discontinuing or modifying allocated interventions {11b}

Participants that develop intolerance to study treatment during the trial will be able to down-titrate to 1 or 2 tablets (500–1000 mg) per day as required without unblinding. Participants, their physicians, investigators and adjudication committee will be blinded to treatment allocation for the duration of the trial. Unblinding will be possible where clinically required using a dedicated Web-based function. Only the Data and Safety Monitoring Board (DSMB) will have routine access to unblinded data prior to trial completion. The study drug will be provided to participants using a pharmacy dispensing service.

#### Strategies to improve adherence to interventions {11c}

The following procedures will be implemented to maximise participants’ adherence to the study treatment:
Participant education during all follow-up interactions which will focus on the importance of taking the study drug, including timing, storage and what to do in the event of a missed doseParticipants will be asked at each follow-up how regularly they take the study drug (every day [about 100% of tablets], nearly every day [about 80–99% of tablets], some days [about 40–79% of tablets], a few days [about 10–39% of tablets], almost never [about 1–9% of tablets] or never [0%]). Reasons for poor or non-adherence will be sought and addressed as far as possible. Participants will also be asked at each follow-up how many tablets are remaining in the bottle/kitParticipants will be provided with the contact details of the responsible researcher so that they can make contact if for any reason they are unable to continue their study drug or have missed multiple doses and are unsure whether to continue

### Relevant concomitant care permitted or prohibited during the trial {11d}

Patients will receive medical management to reduce their cardiovascular event risk and management of any co-morbidities by their treating physician according to current practice guidelines [4, 5].

### Provisions for post-trial care {30}

Following completion of the study, participants will be referred to their primary care provider and treating physician for ongoing management. Post-study follow-up of all participants (off treatment) using electronic registry data will continue for at least 5 years after the database lock, subject to funding availability to study longer term outcomes. No arrangements are in place to provide metformin to participants after the study has completed.

### Outcomes {12}

#### Primary outcome

The primary assessment will compare the number of AAA events (defined as the occurrence of AAA repair or AAA mortality due to rupture) between study groups which were observed during the treatment period. This will be in the form of an intention to treat (ITT) comparison including all randomised participants.

#### Secondary outcomes

Secondary assessments will involve ITT comparisons including all randomised participants to test the effect of metformin versus placebo on the following outcomes:
i*AAA growth assessed by ultrasound*: Current clinical guidelines in every participating country recommend patients with ≥35 mm AAA undergo ultrasound imaging surveillance as part of their standard clinical care [5, 37, 38], which will be used to determine AAA growth over the course of the study. Digital Imaging and Communications in Medicine (DICOM®) AAA ultrasound images will be transferred from participating sites to the coordinating centre at screening and thereafter. The maximum anteroposterior orthogonal outer wall-to-outer wall measurement will be centrally assessed by experienced observers who have previously been shown to have excellent imaging analysis reproducibility. If DICOM images are not available, the maximum anteroposterior orthogonal outer wall-to-outer wall measurement will be measured by a site investigator experienced in reading ultrasound. Linear mixed effects modelling will be used to analyse AAA growth as previously described [39, 40]. If participants undergo imaging by other or additional modalities as part of clinical care, such as CT and/or magnetic resonance imaging, these images will also be collected and used to assess AAA diameter and volume growth independent of ultrasound imaging. If data becomes available from these differing imaging modalities on a sufficient sample of participants, a meta-analysis of the different data sets will be performed.ii*MACE*: Defined as non-fatal myocardial infarction, non-fatal stroke and cardiovascular death (i.e. sudden death, death due to myocardial infarction, valvular heart disease, cardiomyopathy or primary arrhythmia, or other cardiovascular disease or investigations or procedures related to these presentations).iii*Health-related quality of life*: Health-related quality of life will be assessed by generic (short form 36; SF-36) and disease-specific (the Aneurysm-Dependent Quality of Life [AneurysmDQoL]). These assessments will be performed at entry and annually.iv*Requirement for the peripheral vascular surgical procedure*: Defined as lower limb peripheral revascularisation (open or endovascular), carotid artery revascularisation, other aneurysm repair and major amputation. Incidence of the composite event (i.e. first occurrence of any procedure) and total number of events will be examinedv*All-cause mortality* is defined as death from any cause.

#### Exploratory outcomes

Exploratory assessments will investigate other possible beneficial or adverse effects of metformin during the treatment period as well as during planned post-trial follow-up. Exploratory assessments will involve ITT analyses amongst all randomised participants of the effects of allocation to metformin versus placebo during the study period on outcomes including, but not limited to:
iCause-specific mortality including deaths from cardiovascular disease and deaths from cancer and different types of cancersiiDevelopment of diabetes mellitusiiiCancer at all sites (excluding any known to pre-date randomisation and non-melanoma skin cancers) specifically including lung cancer, bowel cancer, bladder cancer and prostate cancerivSymptomatic gout. A tertiary analysis will be performed to examine whether participants randomised to metformin have fewer episodes of gout. Prior observational evidence suggests that metformin could prevent exacerbations of gout through anti-inflammatory effects [41]vCirculating biomarkers of AAA pathology will be assessed in a subgroup of participants who consent and where it is feasible to obtain blood samples for a biomarker sub-studyviRequirement for repeat open or endovascular AAA repair (i.e. re-intervention)

#### Safety assessments

Safety assessments will be performed on the per-protocol and ITT datasets of the effects of allocation to metformin versus placebo during the study period on:
iTotal serious adverse eventsiiLactic acidosisiiiSymptomatic hypoglycaemia

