#### **Methods in analysis to handle protocol non-adherence and any statistical methods to handle missing data {20c}**

A per-protocol analysis is planned focused on participants who regularly took the study drug every day or nearly every day.

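### Safety is to be compared on a per-protocol set selected by adherence, on a par with ITT, with no statement of which analysis governs

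*Protocol article*

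**What the plan says.** *Safety assessments* in the protocol article covers total serious adverse events, lactic acidosis and symptomatic hypoglycaemia. It says: "Safety assessments will be performed on the per-protocol and ITT datasets", and presents both as showing effects of allocation. Neither dataset is given precedence.

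The only definition of the per-protocol set is in section {20c}: "A per-protocol analysis is planned focused on participants who regularly took the study drug every day or nearly every day". No outcome is named there, and nothing is said about how adherence is summarised over follow-up. The adherence categories are in section {11c}. They are self-reported at each follow-up and carry percentages, for example "nearly every day [about 80–99% of tablets". A count of remaining tablets is also requested.

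Section {11b} says that participants with intolerance "will be able to down-titrate to 1 or 2 tablets (500–1000 mg) per day as required without unblinding". The primary aim, in *Objectives {7}*, is to "assess whether a daily dose of 1500 mg metformin extended release (XR) compared to placebo".

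Two further provisions matter. Section {18b} encourages participants who stop drug to stay in follow-up and, with their consent, keeps their data in the ITT analysis. The primary, secondary and exploratory comparisons are all ITT.

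**The concern.** A per-protocol set of this kind is chosen by behaviour after randomisation. For safety, that behaviour can be a consequence of the outcome. A participant who has a reaction to the drug and stops is likely to fail the adherence definition, and may take the event out of the comparison with them. If this happens more often on metformin than on placebo, the per-protocol contrast moves towards no difference.

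The safety sentence also says that both datasets show effects of allocation. Only the comparison of everyone as randomised can show that; an adherence-selected subset cannot.

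At stake is what a reader concludes if the two analyses disagree. With no governing analysis named, a reassuring per-protocol result could be given equal weight to a less reassuring ITT result.

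**Working it through.** **Inputs from the article.** 977 per arm; drop-out 5% per annum, defined as stopping metformin in the intervention group; mean follow-up 3.5 years (all *Sample size {14}*); full allocation three 500 mg tablets a day (section {11a}).

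**The plan's own figure.** The point disputes no stated number, but the drop-out rate also feeds the event target. For a hazard ratio of 0.75, 90% power and two-sided 0.05, Schoenfeld's formula gives 4(1.960 + 1.282)² / (ln 0.75)² = 508 events. Then 508 / (1 − 0.05 × 3.5) = 508 / 0.825 = 615.8, which matches the stated 616. The article does not name this adjustment, so the match is an inference.

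**How many stop metformin by 3.5 years.**

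| Reading of 5% per annum | Formula | Share | Stop, of 977 | Remain |
|---|---|---|---|---|
| Exponential | 1 − exp(−0.05 × 3.5) | 16.1% | 157 | 820 |
| Compound | 1 − 0.95^3.5 | 16.4% | 161 | 816 |
| Linear | 0.05 × 3.5 | 17.5% | 171 | 806 |

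These are stops for any reason. The article does not say how many would be due to harm.

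**Direction of bias, illustrated with assumed figures that are not in the document.** Take a true relative risk of 1.5. Let a share *s* of the excess metformin cases stop and leave the set, and let no placebo participant leave. With placebo risk 10% and *s* = 50%:

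- metformin cases: 0.15 × 977 = 146.6
- cases removed: 0.05 × 0.50 × 977 = 24.4
- per-protocol risk: (146.6 − 24.4) / (977 − 24.4) = 12.8%
- per-protocol relative risk: 1.28, against 1.5 under ITT

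| Placebo risk | *s* = 25% | *s* = 50% | *s* = 75% |
|---|---|---|---|
| 2% | 1.38 | 1.26 | 1.13 |
| 10% | 1.39 | 1.28 | 1.17 |
| 30% | 1.43 | 1.35 | 1.27 |

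**How far this depends on the assumptions.** Suppose instead that a reaction occurs in 3% on metformin and 1% on placebo, that the same share of those affected leaves in both arms, and that about 817 remain per arm.

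- At 80% leaving: 29.3 × 0.20 / 817 = 0.72% and 9.8 × 0.20 / 817 = 0.24%. The excess is about 0.5 points instead of 2.0.
- At 25% leaving: 2.69% and 0.90%. The excess is about 1.8 points.
- In both cases the relative risk stays at 3.0.

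Attenuation of the ratio therefore needs reaction-related stopping to differ between arms. The absolute excess shrinks whenever affected participants leave, by an amount set almost wholly by the assumed share.

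**Down-titrated participants.** Counted against three tablets, one tablet a day is 1/3 = 33%, in the 10–39% band, and two a day is 2/3 = 67%, in the 40–79% band. Both fall outside the per-protocol set. Counted against the reduced number, or by frequency alone, both are fully adherent. The article does not state the denominator.

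**The case against.** The strongest reply is that ITT safety is in the same sentence. Participants who stop are followed with consent, serious adverse events are collected until study completion, events leading to discontinuation are documented, and the data monitoring committee reviews unblinded data regularly. The active run-in should also reduce later stopping for intolerance. All of this stands. A reader might infer that people harmed by the drug vanish from the trial's safety assessment; the document does not support that. They are likely to leave one of two analyses.

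A reader might also infer that someone on a third of the allocated dose counts as adherent. That follows only if adherence is judged by frequency or against the reduced tablet number. Section {11c} ties each category to a percentage of tablets, and against three tablets the same person is excluded. What remains is an unstated denominator.

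A third tempting inference is that the efficacy analysis is compromised. The per-protocol sentence names no outcome, the efficacy comparisons are ITT, and an adherence-defined set is not in itself an error as a supportive analysis. Replacing it with a weighted analysis would be a preference.

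Finally, the article defers detail to an analysis plan that is not shown, and does not say whether events before stopping would be discarded. That limits any statement of size. It does not remove the point, because the article itself puts safety on the per-protocol set beside ITT without ranking them.

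**Conclusion.** The point holds in a limited form. One of the two specified safety analyses uses a set defined by intake after randomisation. It can be biased towards no difference, it does not estimate an effect of allocation, and nothing in the article makes it subordinate to ITT.

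The size of the bias cannot be derived from the document. The only anchor is that 157 to 171 of 977 metformin participants (16 to 17.5%) would stop by 3.5 years for any reason at the planned rate. The relative risks above show direction under assumed inputs and are not predictions. They rest on two assumptions: that those who stop leave the set together with their event, and that reaction-related stopping is more common on metformin.

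The primary result, the 616-event target and power do not change. The treatment of down-titrated participants is a separate ambiguity between sections {11b}, {11c} and {20c}.

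**What to change.** - In *Safety assessments*, name ITT (all randomised, whole study period) as the governing safety analysis.
- Replace the per-protocol safety set with an on-treatment count among all participants who took at least one dose of double-blind drug, counting events up to last dose plus a fixed, pre-stated lag. This keeps the event that led to stopping. Give person-time alongside it, since time on drug may differ between arms.
- Keep the wording about effects of allocation for the ITT analysis only.
- Reconcile sections {11b}, {11c} and {20c} by stating the denominator for the percentage of tablets, and hence whether down-titrated participants count as adherent in any supportive per-protocol analysis.

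The cost is protocol or analysis-plan wording and slightly more analysis. Adherence, serious adverse events and events of special interest are already recorded every 3 months (Table 1). The article does not list a last-dose date; if the case report form lacks one, it needs a field or a rule for deriving it from the 3-monthly contacts.
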